#### **4.2.3 Exclusion of particular populations**

Renal impairment is not expected to significantly alter the elimination of UPA. In the absence of specific studies, UPA is not recommended for patients with severe renal impairment unless the patient is closely monitored.

There is no therapeutic experience with UPA in patients with hepatic impairment, which is expected to alter the elimination of UPA, resulting in increased exposure. This is considered not to be clinically relevant for patients with mildly impaired liver function. UPA is not recommended for use in patients with moderate or severe hepatic impairment unless the patient is closely monitored.

UPA use in women with severe asthma insufficiently controlled by oral glucocorticoids is not recommended.

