| TARGET POPULATION: | 
Women aged over 18 years or over, who are presenting to primary and/or secondary care with HMB.
 
Exclusion criteria:
 
Post-menopausal, a uterus >14 week fibroid uterus and/or cavity length >11cm, submucosal fibroids >2cm in diameter, contraindications to UPA or LNG-IUS; intention to continue current use of CYP3A4 inhibitors (e.g. erythromycin propionate; ketoconazole); intention to continue current use of CYP3A4 inducers (Phenytoin, carbamazepine, rifampicin, St John's Wort), intention to continue current use of P-glycoprotein substrate (e.g. digoxin); past, current or suspected diagnosis of endometrial hyperplasia or neoplasia, severe hepatic impairment; Epilepsy managed with carbamazepine, phenytoin; significant renal impairment; pregnant; current plans to become pregnant within 12 months; currently breastfeeding, severe asthma that is not sufficiently controlled by oral glucocorticoids; past or current known history of uterine, cervical, ovarian or breast cancer; receiving P-glycoprotein substrates; current use progestagen-releasing intrauterine device (except if allocated within UCON), intention to continue continued regular use of Mefenamic acid, intention to continue intention to continue regular use of Mefenamic acid, intention to continue regular use of GnRH analogues, continued regular use of Progestagen-only contraceptive, intention to continue continued regular use of combined oral contraceptive pills, intention to continue hormonal replacement therapy.
 |

|                        |                                                                                                                                                                                                                                                                                                                                                                                                                                                                                                                                                                                                                                                                                                                                                                                                                                                    |

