### **4.2.2 Exclusion Criteria**

- Post-menopausal
- A >14 week fibroid uterus and/or cavity length >11 cm confirmed by ultrasound scan
- Submucosal fibroids >2cm diameter confirmed by ultrasound scan
- Contraindications to UPA or LNG-IUS
- Intention to continue current use of Cytochrome P450 (CYP3A4) inhibitors
- Intention to continue current use of Cytochrome P450 (CYP3A4) inducers (e.g. Phenytoin, carbamazepine, rifampicin, St John's Wort)

- Intention to continue current use of P-glycoprotein substrates (e.g. digoxin)
- A past, current or suspected diagnosis of endometrial hyperplasia or neoplasia
- Severe hepatic impairment
- Epilepsy managed with carbamazepine, phenytoin
- Significant renal impairment
- Pregnant
- Current plans to become pregnant within 12 months
- Currently breastfeeding
- Severe asthma that is not sufficiently controlled by oral glucocorticoids
- Past or current known history of with uterine, cervical, ovarian or breast cancer.
- Current use of progestagen-releasing intrauterine device (except if allocated within UCON)
- Intention to continue regular use of Mefenamic acid
- Intention to continue regular use of Tranexamic acid
- Intention to continue regular use of GnRH analogues
- Intention to continue regular use of Progestagen-only contraceptive
- Intention to continue regular use of any combined oral contraceptive pills
- Intention to continue regular use of hormonal replacement therapy

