### **6.6.1 Liver Injury (unconfirmed adverse reaction currently under investigation)**

Five reports of serious liver injury, including four cases of hepatic failure needing liver transplantation, have been reported worldwide in women using UPA for uterine fibroids.

Women with severe hepatic impairment are excluded from the trial. Participants receiving UPA will undergo monthly liver function tests to monitor for signs of liver injury (see 6.5 for further details).

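### The listed exclusions cover only severe hepatic impairment, although section 4.2.3 advises against UPA in moderate impairment without close monitoring, and no liver test is scheduled before the first dose

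*Protocol*

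**What the plan says.** Section 4.2.3 of the Protocol deals with populations in whom UPA needs caution. On the liver, it states that there is no treatment experience in hepatic impairment and that reduced elimination is expected to raise exposure. It treats only mild impairment as clinically unimportant. It then says: "UPA is not recommended for use in patients with moderate or severe hepatic impairment unless the patient is closely monitored".

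The hepatic exclusion is stated in three places:

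- Section 4.2.2: "Severe hepatic impairment".
- Trial Summary, target population: "severe hepatic impairment; Epilepsy managed with carbamazepine, phenytoin; significant renal impairment".
- Liver Injury section, added in Version 5 and numbered 6.6.1 (a number also used for endometrial changes): "Women with severe hepatic impairment are excluded from the trial".

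On testing, Table 1 (section 7.3) has one liver function row. Its only mark is in the 3-month column, and the footnote attributes it to the Urgent Safety Measure: monthly tests for women now taking UPA and one 2 to 4 weeks after the final dose. Section 8.1.10 repeats this. The screening blood is for haemoglobin and oestradiol (Table 1 and section 8.1.3), and Table 1 notes that it is not a safety sample.

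Sections 5.6.5 and 6.5 stop UPA when transaminases exceed twice the upper limit of normal (2 x ULN).

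**The concern.** Section 4.2.3 makes the use of UPA in moderate impairment depend on close monitoring. The eligibility list does not exclude moderate impairment, and the schedule in force before the safety measure contained no liver monitoring. The advice therefore reaches neither the list that investigators confirm at randomisation nor the assessments that would satisfy its condition.

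Two things are at stake if the trial restarts. The first is entry: women in whom higher exposure is expected could be randomised to a drug under review for liver injury. The second is interpretation, which is a separate matter. Without a transaminase value before the first dose, a raised on-treatment value cannot be reliably told apart from an abnormality that was already there. That weakens the causality assessment required by section 10.4.2.

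**Working it through.** The plan gives no figure on this point and no arithmetic applies. The check sets the provisions side by side.

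**1. Which grades does each provision cover?**

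| Place in the Protocol | Mild | Moderate | Severe |
|---|---|---|---|
| 4.2.3 (advice) | not clinically important | advised against unless monitored | advised against unless monitored |
| 4.2.2 (exclusion) | not named | not named | excluded |
| Trial Summary (exclusion) | not named | not named | excluded |
| Liver Injury, 6.6.1 (exclusion) | not named | not named | excluded |

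All three statements of the exclusion stop at severe. Moderate impairment is the only grade that 4.2.3 warns about and no listed hepatic exclusion covers.

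**2. Does the list decide entry?** Yes. Section 4.2 requires all criteria to be met and each to be confirmed at randomisation. Section 5.6.1 gives no trial number until every eligibility question is answered. A woman with moderate impairment passes the hepatic item.

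**3. Is the monitoring condition met elsewhere?** Not before the safety measure. Table 1 and section 8.1.3 show no liver test at screening or baseline, and every scheduled on-treatment test is tied to that measure. Those tests now monitor women still on a course, but they come after dosing has begun, so they cannot screen.

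**4. Is a conditional warning treated the same way elsewhere in 4.2.3?** The renal advice carries the same condition: "In the absence of specific studies, UPA is not recommended for patients with severe renal impairment unless the patient is closely monitored". Section 4.2.2 nevertheless has an outright exclusion, "Significant renal impairment". That term is not defined; on its natural reading it includes severe impairment. Section 4.2.3 expects no important change in UPA elimination from renal impairment, but does expect one from hepatic impairment. No reason is given for the less complete hepatic exclusion.

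**5. Can the gap act now?** No. Randomisation is suspended (5.6.1) and no new UPA course may begin (6.5). Section 4.2 is, however, not bracketed as a procedure used before the safety measure, so it remains the standing eligibility text.

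**The case against.** The strongest reply is that the hepatic text is a deliberate graded rule: mild is acceptable, moderate is left to the investigator under close monitoring, and severe is excluded. Section 4.2.3 does not require moderate impairment to be excluded. This stands to the extent that the two sections can be read together. A reader might infer a contradiction, and the documents do not support that. The reply does not explain why the monitoring on which the rule depends was never scheduled.

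Second, section 4.2.2 also excludes women with contraindications to UPA. This could catch some moderate cases through the product information kept at site (section 6.1.8). That information is not shown, and 4.2.3 itself words the matter as a recommendation, so the objection stands in part and remains unsettled.

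Third, nobody can enter under Version 5, and a restart would follow the regulatory review and need its own amendment. This stands, and it limits the point to a restart.

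Fourth, the missing baseline test is a different matter from the missing grade. This also stands. ALT and AST do not define moderate impairment, so their absence does not show that moderate cases were missed. Nor is leaving out a liver test before the February 2018 alert shown to have been an error. Attribution is partly covered already, because section 10.3 has the investigator review notes and laboratory reports and section 10.4.2 asks for alternative causes.

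**Conclusion.** The point holds as a gap to be closed before any restart. All three statements of the hepatic exclusion omit a grade that section 4.2.3 warns about, no liver test is scheduled before the first dose, and none was scheduled on treatment before the safety measure.

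A reader might go further and infer that women with moderate impairment were enrolled or harmed, or that current participants are at added risk. The documents support neither. They give no count of such women, and none is estimated here. For women still on UPA, stopping above 2 x ULN, close monitoring and referral where indicated apply whatever the baseline value. For them the missing baseline affects attribution only.

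The conclusion assumes that the product information does not already exclude moderate impairment. It also assumes that the patient-pathway figures and trial schema, which are not shown, add no earlier liver test to what the text and Table 1 describe. Confidence is medium for these reasons.

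**What to change.** Make two changes in the amendment that a restart would need anyway.

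1. **Eligibility wording.** In 4.2.2, the Trial Summary and the Liver Injury section, widen the hepatic exclusion to moderate or severe impairment, or to something stricter if the regulator requires it.
2. **Baseline test, as a separate point.** Add ALT and AST to the blood already drawn at screening, with an entry limit no higher than 2 x ULN, so that no woman is admitted who already meets the stopping rule. The purpose is a reference value for that rule and for causality assessment, not a way of grading impairment.

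The cost is three wording changes, one added assay on an existing sample and slightly narrower entry.

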### **4.3 CO-ENROLMENT**

Women randomised to the UCON trial should be excluded from participation in any further trial of investigational medicinal products (IMPs) for the treatment of gynaecological disorders or infertility. If the woman has withdrawn from the trial treatment but is still contributing to data collection, any further treatments within trials for her HMB should be noted, for example if she chooses to participate in a trial of surgery for HMB.

Women already participating in another trial of an IMP for a non-gynaecological reason are able to participate in UCON, provided careful consideration of the interactions between that IMP and the

UCON trial treatments is undertaken. Arrangements for co-enrolment with another CTIMP will be bound by a written agreement between the Chief Investigator and Co-Sponsors of both/all CTIMPs implicated. This agreement will include special safety reporting measures if required; a minimum wash-out period between last dose in one study and first dose in another; a statement to indicate that the chairs of the TSC/DMC from each study and statisticians from each study that they have no objections to the proposals for co-enrolment; and a statement that arrangements for attribution of liability for co-enrolled participants have been put in place agreed between the sponsors of both/all CTIMPs implicated.

## **5 PARTICIPANT SELECTION AND ENROLMENT**

### **5.1 IDENTIFYING PARTICIPANTS**

**Recruitment for the trial has been suspended until further notice on account of a USM requirement from the MHRA (12th February 2018).**

[Procedure adopted prior to USM: Patients will be recruited from the gynaecological, outpatient clinics of participating centres (identified in both primary and secondary care), fitting around their current service provision. Figure 1 shows the different routes by which women may be identified and approached.]

#### **5.1.1 Identification from GP databases**

**Recruitment for the trial has been suspended until further notice on account of a USM requirement from the MHRA (12th February 2018).**

[Procedure adopted prior to USM: Patients with a history of HMB problems may be identified within GP practices. Databases will be screened using the HMB related Read codes, with access to these patient identification centres negotiated via the local Primary Care Network. The GP practices will send potentially eligible women a patient invitation letter, which will include a copy of the preliminary patient leaflet. The invitation letter will include the local contact details of the UCON research nurse, who can discuss the trial over the phone and if the patient is eligible make a hospital appointment. Once a hospital appointment is made, a letter confirming the appointment will be sent to the patient, which will include a patient information sheet.]

##### **5.1.1.1 Raising awareness of the trial through community pharmacies**

**Recruitment for the trial has been suspended until further notice on account of a USM requirement from the MHRA (12th February 2018).**

[Procedure adopted prior to USM: The Primary Care Network aim to reach out to as many patients as possible and this includes raising awareness of research through posters and leaflets in community pharmacy. Given patients with a history of HMB do not regularly present at their GP practice, UCON trial posters will be displayed in community pharmacy that have been selected by the Primary Care Network. The poster will include brief information about the trial and provide local contact details of the UCON research nurse. Patients can discuss the trial over the phone and if the patient is eligible the UCON research nurse will make a hospital appointment. Once a hospital appointment is made, a letter confirming the appointment will be sent to the patient, which will include a patient information sheet.]

### **5.1.2 GP Referral to Secondary Care**

**Recruitment for the trial has been suspended until further notice on account of a USM requirement from the MHRA (12th February 2018).**

[**Procedure adopted prior to USM:** Patients with existing HMB problems who present to a GP may then be referred to a participating hospital. GP practices in the catchment area of the participating centres will be made aware of the study and will be encouraged to discuss the trial with the woman, explaining a referral will be necessary. The UCON research nurse(s) will screen all patient referral letters to identify referred participants who have been introduced to the trial and arrange a gynaecology clinic appointment. Once a hospital appointment is made, a letter confirming the appointment will be sent to the patient, which will include a patient information sheet.]

### **5.1.3 Gynaecology Clinic Patient Identification**

**Recruitment for the trial has been suspended until further notice on account of a USM requirement from the MHRA (12th February 2018).**

[**Procedure adopted prior to USM:** The UCON research nurses will screen the patient referral letters who have been referred by their GP to secondary care but who have not been introduced to the trial. Eligible patients will then receive a patient invitation letter along with a copy of the participant information sheet and be invited to contact the UCON research nurse to discuss the trial and/or make a hospital appointment. Once a hospital appointment is made, a letter confirming the appointment will be sent to the patient, which will include a patient information sheet.]

Please note, recruitment for the trial has been suspended until further notice on account of a USM requirement from the MHRA (12th February 2018).

Figure 1: Identification and screening of participants for the UCON trial

[figure not shown]

## 5.2 CONSENTING FOR SCREENING FOR ELIGIBILITY

**Recruitment for the trial has been suspended until further notice on account of a USM requirement from the MHRA (12th February 2018).**

[Procedure adopted prior to USM: All women who are referred to secondary care with HMB will be identified by the UCON research nurse(s) in each centre as a potential participant, prior to her outpatient appointment. The gynaecologist who will be providing her clinical care will discuss treatment options and establish eligibility based on history and preferences. The option to contribute to the mechanistic sub-study will instead be discussed in those centres able to contribute to the sub-study. Women who are confirmed pregnant are not eligible for the trial and participants would need to be prepared to avoid pregnancy for one year, so a discussion must be held about intentions to conceive.]

Consent to participate in UCON will be sought by the gynaecologist, and/ or by a research nurse. Women will be asked to consent to the UCON Trial in order that trial specific procedures, namely endometrial assessment using transabdominal and/ or transvaginal ultrasound and outpatient endometrial biopsy, can be undertaken. Women will be asked to confirm their consent by initialling the appropriate boxes on the consent form and signing in the presence of the person taking consent. Multiple copies will be available to ensure a copy is given to the women, one is kept in the patient notes, one in the local site file and one is sent to the UCON Trial Office.

Women who consent at this point should have the ultrasound(s) performed and biopsy taken at the same clinic appointment if at all possible. If a patient had an adequate ultrasound within the previous 3 months of the date of the baseline visit, and is documented in the clinical case records (medical notes), then the results may be used to determine eligibility within the UCON trial. The relevant member of the site team should complete an Ultrasound Form and send to the UCON Trial Office.

If a patient has confirmed submucosal fibroids >2cm at the screening ultrasound but is subsequently contraindicated by hysteroscopy (requested as part of standard clinical care pathway), this may confirm eligibility at the baseline visit.

All women should be given a menstrual blood loss diary containing the PBAC to take away and complete during their next period, which ideally will occur before the next gynaecology clinic appointment. The completed blood loss diary will need to be returned at the baseline visit prior to randomisation.

At the Royal Infirmary of Edinburgh the option of participating in addition in the mechanistic sub-study and undergoing additional endometrial biopsies and/ or MRI scans should be discussed. Women should be advised that these additional assessments are only applicable if they are randomly allocated to UPA.

All women approached should be recorded on the screening log(s), available in the investigator site file. This information will only be passed to the coordinating centre as an anonymous screening log.]

## 5.3 RE-CONSENTING PARTICIPANTS FOLLOWING THE USM

Participants actively taking UPA at the time of the USM will be permitted to complete their current 12 week course. In such cases, participants must be re-consented at their next visit (using updated participant information) to demonstrate that the updated safety information and additional blood tests have been discussed.

Alternatively participants may choose to stop UPA treatment – these participants do not need to re-consent .

#### **5.4 CONFIRMATION OF ELIGIBILITY BEFORE RANDOMISATION/ ENTRY INTO THE MECHANISTIC SUB-STUDY**

**Recruitment for the trial has been suspended until further notice on account of a USM requirement from the MHRA (12th February 2018). Recruitment to this component of the study is already completed.**

**[Procedure adopted prior to USM:** The participant should be invited to a baseline gynaecology clinic appointment by which time the results of the endometrial biopsy must be available. If a patient had an adequate endometrial biopsy within the previous 6 months of the date of the baseline visit, and is documented in the clinical case records (medical notes), then the results may be used to determine eligibility within the UCON trial. The relevant member of the site team should complete a Local Endometrial Biopsy Evaluation Form and send to the UCON Trial Office.

Normal findings from the local histopathology service will confirm eligibility for UCON, which should be relayed to the woman and continued consent established. At this point, the menstrual diary should be collected, if the woman has had a period in between appointments, and the other baseline questionnaires should be completed in clinic at this time.

Any pathological or suspicious findings from the biopsy should be investigated thoroughly and treated as appropriate outside of the UCON trial. ]

#### **5.5 INELIGIBLE AND NON-RECRUITED PARTICIPANTS**

**Participants who were consented prior to 12 February 2018 but were not randomised will have the reason for suspension of randomisation explained.**

**Such participants will return to routine care and an alternative treatment option for managing their complaint of HMB will be offered.**

**[Procedure adopted prior to USM:** If a woman is screened but is not eligible for the trial due to a preference, contraindication or pathological reason for their HMB, or consent for randomisation is not given, an anonymous record of the case should be kept in the screening log. The screening log will include, age group, ethnic group, and the reason each patient not eligible for the trial. Women who consent and have an ultrasound and endometrial biopsy but are then found to be ineligible will be noted. The screening log should be kept in the site file and a copy sent to the UCON Trial Office, who will be able to identify women based on the information provided. This screening log information will inform updates to the funder regarding recruitment targets for UCON. ]

